### Data management

The OTN, GeriMedRisk clinical database, and pharmacy and electronic medical records are independently managed on secure servers. We will access these databases with encrypted password-protected computers stored in locked cabinets in a secure office. Qualitative study surveys to the referring clinicians, non-referring but eligible clinicians, and GeriMedRisk staff will be administered electronically, data will be de-identified, password-protected, and stored securely. No patient information will be included in the survey. Interviews will be recorded, and data analysis will be stored electronically as a password-protected document on a password-protected encrypted computer in a locked room.

### Statistical data analysis

#### Quantitative analysis

As the main objective of this study is to evaluate the feasibility of GeriMedRisk and its stepped-wedge cluster randomized trial design, we will describe the primary outcomes in a narrative analysis with 95% confidence intervals (CI) where appropriate. We define success or acceptability of GeriMedRisk as a composite of either 60% adherence to GeriMedRisk recommendations or at least 20% of each LTC sites’ physicians making more than one consult to GeriMedRisk during the study period (May 1, 2017, to December 31, 2017).

For the secondary outcomes, we will assess each LTC site’s outcomes, described as monthly rates, in the 12 months preceding the intervention (baseline) between clusters pre-intervention and calculate the intercluster variance. We will assess for intra- and intercluster differences in the secondary outcomes, described as each LTC site’s monthly rates, with weighted generalized linear mixed models. This definition will guide our interpretation of the study’s results and potential modifications to the GeriMedRisk intervention or subsequent larger efficacy trial’s protocol.

#### Sample size calculation

As this is a feasibility study, the primary outcomes include recruitment, acceptability, and time required for the intervention. We used the methods described by Hemming et al. to calculate the sample size for stepped-wedge cluster randomized controlled trials. While the current risk of adverse events at these sites is currently unknown, the emergency department visits rate for LTC in Ontario, Canada, is 25% [34]. Although LTC clinicians are the users of the intervention, patient outcomes remain of interest, particularly for the larger efficacy trial. In order to detect a decrease in ED visits by 20%, with four steps and one cluster introduced per step and a total sample size of 628 LTC patients, we estimate 181 patients per cluster for 80% power and 5% significance [36]. We estimate conservatively that we will need to have consults from 20% of each LTC’s clinicians (physicians, pharmacists, and nurse practitioners). The results of this study will inform our sample size calculation for the future larger efficacy trial.

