### Setting

We will conduct this study across a convenience sample of four LTC facilities in the Waterloo-Wellington region, Ontario, Canada, with each site serving as a cluster. The Waterloo-Wellington region has a population exceeding 775,000 residents and encompasses the major urban centers of Waterloo, Kitchener, Cambridge, and Guelph. While 90% of the geography is rural, 90% of the population lives in urban areas. The population of Waterloo-Wellington has similar demographics as the rest of the province of Ontario [21]. At each site, residents are assigned to a primary care doctor or nurse practitioner. Each site is supported by a consultant pharmacist who performs medication reviews at full-time equivalents ranging between 0.25 and 0.3. The three Schlegel Village LTC homes have uniform physical environments and philosophies of care but individualized staffing and clinical programs. University Gates Schlegel Village is a 192-bed LTC home located in Waterloo, supported by primary care clinicians and regular on-site geriatric medicine and geriatric psychiatry consultants. Winston Park Schlegel Village located in Kitchener is a 95-bed facility supported by a primary care clinician and an on-site geriatrician consultant. Riverside Glen Schlegel Village is a 192-bed LTC home located in Guelph that does not have designated support from a geriatrician. LTC patients that require a geriatrician are referred through a centralized intake process through the Waterloo Wellington Specialized Geriatrics Services. St. Joseph’s Health Centre Guelph, a non-profit 244-bed facility, is supported by primary care physician and an on-site consultant geriatrician.

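### The stated total (628) and per-cluster size (181) contradict each other, both match bed counts, and the 80% power attached to them cannot be reproduced

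*Protocol article*

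**What the plan says.** The Sample size calculation section takes as its control rate that "the emergency department visits rate for LTC in Ontario, Canada, is 25" per cent. It sets the target with the words "In order to detect a decrease in ED visits by 20" per cent and describes the design as "with four steps and one cluster introduced per step". It then reports "a total sample size of 628 LTC patients, we estimate 181 patients per cluster for 80% power and 5% significance".

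The Setting section names four homes, each a cluster. Two have 192 beds, one "is a 95-bed facility supported by a primary care clinician", and the fourth is "a non-profit 244-bed facility, is supported by primary care physician and an on-site consultant geriatrician".

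The article does not say whether the 20% is relative or absolute, what period the 25% covers, whether the test is one- or two-sided, whether 181 is per cluster or per cluster-period, or what ICC was used.

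**The concern.** The total and the per-cluster figure disagree by almost 100 residents in a trial with only four clusters. Each can be rebuilt from the bed counts, but from different sets of homes. That raises the question whether either number came out of a power calculation. If not, the 80% has no visible basis.

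The stake is how the ED-visit comparison will be read. A reader who accepts 80% power may give a null ED result more weight than the design supports. Whether the stepped-wedge design can evaluate the service is itself one of the feasibility questions, so the figures describing it should be coherent.

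**Working it through.** **1. Consistency of the stated figures.** 4 × 181 = 724, not 628. 628/4 = 157, not 181.

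**2. Comparison with the bed counts (Setting).**
- All four homes: 192 + 95 + 192 + 244 = 723, and 723/4 = 180.75, which rounds to 181.
- Without the 95-bed home: 192 + 192 + 244 = 628. No other combination of homes gives 628.

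**3. Attempt to reproduce 80% power, relative reading (25% to 20%).**

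Inputs from the article: 25% control rate, 20% decrease, four clusters, one crossing over per step, 5% significance. Assumptions: two-sided test, ICC 0 to 0.1, a new cross-section of residents in each period, and five periods (one all-control period, then T0 to T3).

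The Hussey–Hughes variance of the effect is

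Var = Iσ²(σ² + Tτ²) / [(IU − W)σ² + (U² + ITU − TW − IV)τ²],

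with I = 4, T = 5, U = 10, W = 30, V = 30. Then IU − W = 10 and U² + ITU − TW − IV = 100 + 200 − 150 − 120 = 30. With mean proportion 0.225, p(1 − p) = 0.1744, σ² = 0.1744(1 − ICC)/m and τ² = 0.1744 × ICC, where m is residents per cluster-period. Power = Φ(0.05/SE − 1.96).

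- m = 181, ICC 0: Var = 0.4 × 0.1744/181, SE = 0.0196, z = 2.55, power 72%.
- m = 181, ICC 0.05: σ² = 0.000915, τ² = 0.00872, SE = 0.0245, z = 2.04, power 53%.
- m = 181/5 = 36.2 (181 per cluster in total), ICC 0: SE = 0.0439, z = 1.14, power 21%.
- m = 36.2, ICC 0.05: SE = 0.0536, z = 0.93, power 15%.

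| Residents | ICC 0 | 0.001 | 0.01 | 0.05 | 0.1 |
|---|---|---|---|---|---|
| 181 in every cluster-period | 72% | 63% | 53% | 53% | 55% |
| 181 per cluster in total | 21% | 20% | 16% | 15% | 15% |

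Reaching 80% needs about 219 per cluster-period at ICC 0 (0.4 × 0.1744/(0.05/2.80)²) and about 287 to 349 at ICC 0.001 to 0.1. Using 157 in place of 181 lowers power further (48–66% per cluster-period). With four periods instead of five, 181 per cluster-period gives 72% at ICC 0 and about 46–48% at ICC 0.01 to 0.1.

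Two other routes also miss the stated figures. An individually randomised comparison needs 1,094 per group, and 628 in total would give 32% power. The Woertman design effect gives about 925 to 1,367 patients in total.

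**4. Absolute reading (25% to 5%).** The mean proportion is 0.15, so p(1 − p) = 0.1275. At m = 36.2 and ICC 0, SE = 0.0375, z = 0.20/0.0375 = 5.3, and power is above 99%. It stays above 99% for ICC up to 0.1 in the five-period model. The requirement for 80% power is only about 10 to 20 per cluster-period (at ICC 0, 0.4 × 0.1275/(0.20/2.80)² = 10). So 181 is not the requirement on this reading either.

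**5. Variants that pass 80% on the relative reading.** None is stated in the article.
- One-sided 5% test, ICC 0, 181 per cluster-period: 82%.
- The same residents measured repeatedly, individual autocorrelation 0.6 and cluster autocorrelation 1: 83–91%.
- Twenty monthly periods including the 12-month look-back, 25% taken as a monthly rate, cluster autocorrelation 1: 90–95%.

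In the other direction, if 25% is an annual rate, power falls to about 11–15%. In none of these is 181 or 628 the number that yields 80%.

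**The case against.** The strongest reply is that the power shortfall depends on assumptions the article does not make. This stands. A reader might infer that neither figure can deliver 80% power. The documents do not support that: an absolute 20-point drop gives more than 99%, and step 5 shows other routes past 80%. RAI-MDS 2.0 is applied to all residents quarterly, so repeated measurement of the same residents is plausible.

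The bed-count origin is also an inference, because the article never gives the source of 628 or 181. Two exact matches make it a strong one. A reader might go further and say that the 95-bed home cannot supply 181 residents. That is not established: 181 is not tied to a period, the observation window includes a year of look-back, and no turnover figure is given. Nor can one say that the required size always exceeds the largest home, since about 219 at ICC 0 is below 244.

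A condensed article may leave the ICC and the time base to the full protocol, so their absence alone is not an error. They matter here because the printed result cannot be reproduced without them.

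Finally, the primary outcome is feasibility and acceptability, ED visits are secondary, and the Study design section already describes an exploratory framework. A reader might fear that 628, 181 or 25% will pass into the 14-home efficacy trial. The article says only that this study's results will inform that calculation, and it plans to estimate the intercluster variance from its own data. None of this removes the contradiction between the two printed numbers.

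**Conclusion.** The point holds in this form. The total and per-cluster sizes contradict each other (628 against 724), which needs no assumption. Both appear to be available beds, and neither was reproduced as the requirement for 80% power.

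The claim of 80% is too optimistic if the decrease is relative, the test two-sided and the model the standard cross-sectional one with five periods and ICC 0 to 0.1: about 53–72% or 15–21%, depending on what 181 counts. It is exceeded if the decrease is absolute. Which case applies cannot be settled from the article. Severity is moderate: a stated design figure is wrong as written, but it concerns a secondary outcome in a feasibility trial.

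**What to change.** In the Sample size calculation section, replace 628 and 181 with 723 beds in four homes, ranging from 95 to 244 per home. State whether the 20% decrease is relative or absolute, the period the 25% refers to, whether the test is one- or two-sided, and the ICC used. Then either give the power the design has under those inputs, or remove the 80% claim and present the ED-visit comparison as exploratory, in line with the framework already named under Study design.

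This is a change of wording only and needs no extra residents. The cost is that the stated power may become less favourable.

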#### Qualitative analysis

For our qualitative analysis, digital recording of the semi-structured interviews will be transformed into verbatim transcripts. Transcripts will be independently reviewed by two members of the research team and analyzed with the purpose of addressing the interview questions. Thematic analysis will be applied to qualitative data from all data collection methods (surveys, interviews, notes) to identify main ideas and themes that cross participant groups (physicians, nurses, pharmacists, GeriMedRisk staff). Quotes that are representative of typical statements given by participants will be extracted to support the themed interpretations. Descriptive data analyses (frequencies: counts, percents, means, SDs, minima, maxima) will be used to describe closed-ended survey data.

We will describe the challenges and accompanying solutions and decision-making process encountered during the study period. These will be informative during our study design process for the future efficacy trial protocol.

### Harms

During our follow-up calls, we will actively collect, assess, report, and manage solicited and spontaneously reported adverse events and other unintended effects of the trial intervention or trial conduct. These include adverse drug events that occur as a result of GeriMedRisk’s suggestions.

### Knowledge dissemination

We plan to disseminate the results of this study in a high-impact peer-reviewed journal within 1 year after the trial end date. We will also share the results with our partners, public and patients, and relevant stakeholders. We will not use professional writers. All authors will fulfill authorship guidelines as defined by the International Committee of Medical Journal Editors. We consulted patients from the community and LTC about GeriMedRisk throughout its conception, study design, and materials (opt-out flyer).

## Discussion

If GeriMedRisk is a feasible intervention, it would be the first technology-based interdisciplinary geriatric pharmacology intervention in Canada. The risks of participating in this GeriMedRisk study include the clinician participant’s time involved for each consult and follow-up. Although each consult may take up to 45 min on the telephone, this time could be significantly decreased by contacting GeriMedRisk through the secure OTN eConsult platform. The benefits of participating in this study include access to geriatric pharmacology expertise in a timely fashion without patient travel to an urban academic health center. Participants will also have the opportunity to provide feedback about GeriMedRisk to help improve the service and its impact on real-world practice. Finally, participants will have access to a service that supports their continuing professional development through concise learning materials pertinent to their patients and quarterly summaries of their learning issues generated from their consults. There will be no cost to participants for these services. By understanding the experiences and perceptions of GeriMedRisk stakeholders, we will be able to provide generalizable information about feasibility and acceptability for the wider health community, refine both referral criteria and mode of delivery for the subsequent clinical trial, inform the potential rollout of the intervention to other healthcare sectors, and further develop the consultation service.

## Abbreviations

ADE: Adverse drug event
CI: Confidence interval
LTC: Long-term care
OTN: Ontario Telemedicine Network
RAI-MDS: Resident Assessment Index Minimum Data Set
